# Can low-dose methotrexate reduce effusion-synovitis and symptoms in patients with mid- to late-stage knee osteoarthritis? Study protocol for a randomised, double-blind, and placebo-controlled trial

**DOI:** 10.1186/s13063-020-04687-3

**Published:** 2020-09-16

**Keywords:** Methotrexate, Osteoarthritis, Effusion-synovitis, Pain

## Abstract

**Background:**

Osteoarthritis (OA) is a common chronic disease in older adults. Currently, there are no effective therapies to reduce disease severity and progression of knee OA (KOA), particularly in mid- to late-stages. This study aims to examine the effect of methotrexate (MTX) on knee effusion-synovitis and pain in symptomatic patients with mid- to late-stage KOA.

**Methods/design:**

This protocol describes a multicentre randomised placebo-controlled clinical trial aiming to recruit 200 participants with mid- to late-stage symptomatic KOA and with effusion-synovitis grade of ≥ 2. Participants will be randomly allocated to the MTX group (start from 5 mg per week for the first 2 weeks and increase to 10 mg per week for the second 2 weeks and 15 mg per week for the remaining period if tolerated) or the placebo group. Primary outcomes are effusion-synovitis size measured by magnetic resonance imaging (MRI) and knee pain assessed by visual analogue scale (VAS). Secondary outcomes are signal intensity alteration within infrapatellar fat pad (IPFP) and Western Ontario and McMaster Universities Osteoarthritis Index (WOMAC) total score and subscores, and the Outcome Measures in Rheumatology Arthritis Clinical Trials-Osteoarthritis Research Society International (OMERACT-OARSI) responders. Both intention-to-treat and per-protocol analyses will be performed.

**Discussion:**

If MTX intervention can relieve symptoms and reduce inflammation in patients with mid- to late-stage KOA, it has the potential for significant clinical and public health impact as this low-cost and commonly used intervention would delay the time to knee replacement, leading to substantial cost savings and improve quality of life.

**Trial registration:**

ClinicalTrials.gov NCT03815448. Registered on 21 January 2019.

## Introduction

Osteoarthritis (OA) is one of the commonest chronic conditions in older people. It is characterised by gradual loss of articular cartilage and changes of other joint tissues, eventually leading, in some cases, to total joint replacement [1]. Approximately 25% of people over 55 years old have had knee pain on most days in a month in the past year. Of these, about half have radiographic knee OA (KOA) and are considered to have symptomatic KOA [1]. In China, the prevalence of symptomatic KOA was estimated up to 8.1% among people of 45 years and older [2]. There are more than 1 million hip or knee replacements every year in the USA, and the number is continuing to rise [3]. The costs of treating OA are expected to grow with our increasing ageing population.

Current treatments for knee OA are limited as there are no effective therapies to reduce disease severity and progression of knee OA particularly in mid- to late-stages [4]. People with mid- to late-stage OA often live with severe pain and have significant difficulty to perform daily activities [5], leading to substantial physical and mental health consequences and diminished quality of life [6]. There is, therefore, an urgent need to find better ways to manage symptoms and disease progression in mid- to late-stage OA.

There are a number of different phenotypes with different etiologies [7]. One is manifested by the presence of synovitis [8]. Pathological studies have shown that synovitis presence is associated with alterations in the adjacent cartilage that are similar, though to a lesser extent, to those seen in rheumatoid arthritis (RA) [9]. Joint effusion shown on non-contrast enhanced T2- or proton density-weighted MRI reflects a composite of true joint effusion (i.e. joint fluid) and synovial thickening [10], which has been regarded as effusion-synovitis. MRI-detected effusion-synovitis strongly predicted the development of incident radiographic OA over 4 years in the Osteoarthritis Initiative (OAI) study [11]. Suprapatellar pouch effusion-synovitis grade or maximal area was associated with increased knee pain, loss of knee cartilage volume, and increase in cartilage defects and bone marrow lesions (BMLs) [12, 13].

Low-dose methotrexate (MTX) administered weekly is commonly prescribed in patients with inflammatory arthritis including RA due to its anti-inflammatory effect and has good long-term safety [14]. There is evidence that low-dose MTX may have beneficial effects on OA via a variety of mechanisms. In a lapine model of OA, treatment with MTX for 12 weeks significantly reduced cartilage lesions in the femoral condyles [15]. In a single-centre, open-label study with 30 knee OA patients, MTX treatment (commenced from 7.5 mg, increasing up to 20 mg at 6 weeks) for 24 weeks significantly reduced knee pain assessed by visual analogue scale (VAS) and the Western Ontario and McMaster Universities Osteoarthritis Index (WOMAC); its analgesic efficacy was comparable to that achieved with NSAIDs and even opioids [16]. A recent multicentre randomised, double-blinded, placebo-controlled trial recruited 155 patients with symptomatic knee OA to examine if MTX treatment (*20–25 mg weekly*) for 6 months could reduce symptoms and disease progression. Preliminary results showed that compared with placebo, MTX modestly reduced knee pain assessed using Numeric Rating Scale, but had no effects on WOMAC knee pain [17]. It had no effects on MRI-assessed knee synovitis [17]. However, this clinical trial has some limitations: (1) the primary outcome evaluation was short (6 months) and may not be long enough to observe disease progression, (2) patients were not selected on the basis of the presence of inflammation, and (3) synovitis was not used as the primary and/or secondary outcomes.

Thus, taken together, there is evidence to suggest that MTX treatment is associated with reduced joint effusion and knee pain, indicating that MTX may have disease-modifying as well as symptom-relieving effects on knee OA. MTX may be particularly acceptable to those with mid- to late-stages of knee OA and joint effusion-synovitis, who have failed other OA therapies.

## Methods and design

### Trial aims

#### Primary aims

The primary aim is to examine, in a randomised, double-blind, and placebo-controlled trial over 52 weeks, whether low-dose MTX reduces knee joint effusion-synovitis and VAS pain compared to placebo in patients with mid- to late-stage knee OA and effusion-synovitis.

#### Secondary aims

The secondary aim is to examine, in a randomised, double-blind, and placebo-controlled trial over 52 weeks, whether low-dose MTX reduces IPFP signal intensity alteration (Hoffa’s synovitis); improves WOMAC pain, function, and stiffness; and has higher OMERACT-OARSI responders compared to placebo in patients with mid- to late-stage knee OA and effusion-synovitis.

#### The primary hypotheses

Compared to placebo, MTX treatment (up to 15 mg per week) over 52 weeks in patients with mid- to late-stage knee OA and effusion-synovitis will:
Reduce joint effusion-synovitis size assessed by MRIImprove knee pain assessed by VAS

#### The secondary hypotheses

Compared to placebo, MTX treatment (up to 15 mg per week) over 52 weeks in patients with mid- to late-stage knee OA and effusion-synovitis will reduce IPFP signal intensity alteration (Hoffa’s synovitis) assessed by MRI; improve WOMAC pain, function, and stiffness; and have higher proportion of OMERACT-OARSI responders.

### Study design

This study is designed as a multicentre, randomised, double-blind, placebo-controlled trial over 52 weeks. The study will be conducted with adherence to the CONSORT guidelines. Two hundred participants from academic hospitals with mid- to late-stage symptomatic knee OA and effusion-synovitis will be recruited and randomly allocated to the treatment or placebo control group. The recruitment strategy will include collaborations with specialist rheumatologists from the following 9 sites: Zhujiang Hospital of Southern Medical University, Peking Union Medical College Hospital, Peking University People’s Hospital, Beijing Hospital, 3rd Affiliated Hospital of Sun Yet-Sen University Guangzhou, Xuanwu Hospital of Capital Medical University, the First Affiliated Hospital of Anhui Medical University, Guangdong Second Provincial General Hospital, and the First Affiliated Hospital of Harbin Medical University. Ethical approval has been received from Ethics Committee of Zhujiang Hospital of Southern Medical University (reference number: 2018-FSMYK-001).

### Participants

At screening, participants will complete questionnaires, clinical examinations, blood tests (blood cell counts, liver function, renal function, hepatitis B/C tests), and chest X-ray and have a knee X-ray and MRI to ensure the inclusion/exclusion criteria are met. The index knee will be defined as the one with symptomatic OA; if both are symptomatic, the one with more severe knee symptoms will be used as the index knee. There will be 7 study visits (screening, baseline, and weeks 4, 12, 24, 36, and 52) (Fig. 1). The study measures are shown in Table 1. If the participant withdraws after a minimum of 24 weeks’ treatment, he/she will be requested to have a second knee MRI scan.

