***Primary outcomes***								
MRI (effusion-synovitis volume)	✔						✔	✔
Knee pain (VAS)	✔		✔	✔	✔	✔	✔	✔

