### Randomisation/blinding

Allocation of participants will be based on computer-generated random numbers using block randomisation. To control for variation in centres, the randomisation will be stratified according to the centres. The RCT will be blinded to participants, investigators, and those measuring the effect of the intervention. Allocation concealment will be ensured by the use of a central automated allocation procedure, with security in place to ensure allocation data cannot be accessed or influenced by any person. Participants will be assigned to the interventions after baseline screening. Sequentially numbered and sealed opaque envelopes which reveal random numbers will be provided to the centres. Identical drugs for each participant will be allocated by research nurse base on the corresponding random number. Objective measures of knee structural changes and knee pain will be made by trained observers who are blinded to group allocation. The statistician who performs the statistical analyses will also be blinded. Unblinding will be allowed in emergency that affects the safety of participants. We will withdraw the unblinded participants but will continue to follow-up as per planned schedule.

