#### Assessment of MRI structural changes

Knees will be imaged in the sagittal plane on a 3.0-T whole-body magnetic resonance unit with use of a commercial transmit-receive extremity coil. T2-weighted fast spin-echo and fat-saturated T1-weighted spoiled gradient echo sequences will be used. Changes in effusion-synovitis and IPFP signal intensity measures from baseline to week 52 are the endpoints, but we will also assess changes in total scores of cartilage defects and BMLs.
*Knee joint effusion-synovitis:* Knee effusion-synovitis maximal volume/area [13] at suprapatellar pouch will be measured at screening and week 52, and severity will be scored from 0 to 3 according to the estimated maximal distension of the synovial cavity by assessing the amount of intra-articular fluid-equivalent signal on T2-weighted MRI [21]. Effusion-synovitis at central portion, posterior femoral recess, and subpopliteal recess will also be assessed.*IPFP signal intensity alterations:* Signal intensity alterations within IPFP were defined as discrete areas of increased signal. Standard deviation of IPFP signal intensity[sDev(IPFP)] and Clustering Factor(H) will be used to represent the signal intensity alteration within IPFP. The measurements will be performed using sagittal planes of fat-saturated T2-weighted images [22] at screening and week 52.

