### Statistical analysis plan

Intention-to-treat and per-protocol (for patients who have taken > 80% the study medication) analyses of primary and secondary outcomes will be performed. The changes in outcome measures among all randomised participants at 52 weeks will be used for intention-to-treat analyses. Independent *t* tests and chi-square tests will be used to examine baseline characteristics of participants between groups. General linear mixed models to account for the effects of clustering by trial sites will be used to compare changes in outcomes in univariable and multivariable modelling between groups. Additional adjustment for imbalanced baseline factors will be made for further analyses. Baseline data will be used for data imputation assuming missing at random. A 95% confidence interval not including the null point or a *p*-value < 0.05 (two-tailed) will be considered statistically significant.

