### Withdrawal

All participants are able to withdraw at any time of the trial. The time and reason will be recorded. If participants withdraw after 6 months of follow-up, we will attempt to obtain their final MRI scans and pain levels.

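### A second MRI is sought from withdrawals only after about 24 weeks or 6 months, although the ITT analysis promises 52-week change in all randomised participants and Table 1 sets no such limit

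*Protocol article*

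**What the plan says.** All references are to the protocol article.

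- **Participants:** "If the participant withdraws after a minimum of 24 weeks" of treatment, a second knee MRI is requested. The condition counts time on treatment.
- **Withdrawal:** "If participants withdraw after 6 months of follow-up, we will attempt to obtain their final MRI scans and pain levels". The condition counts time in follow-up and covers pain as well as MRI. No date is given for the scan.
- **Table 1:** the row beginning "MRI (effusion-synovitis volume" is ticked at screening, at week 52 and in a separate Withdraw column. The Withdraw tick carries no time condition. VAS pain is also ticked there, and at weeks 4, 12, 24, 36 and 52.
- **Assessment of MRI structural changes:** suprapatellar effusion-synovitis "will be measured at screening and week 52, and severity will be scored from 0 to 3". No intermediate MRI is scheduled.
- **Statistical analysis plan:** "The changes in outcome measures among all randomised participants at 52 weeks will be used for intention-to-treat analyses". On missing values: "Baseline data will be used for data imputation assuming missing at random".
- **Randomisation/blinding:** "We will withdraw the unblinded participants but will continue to follow-up as per planned schedule". This is the only place where the article states that follow-up continues on schedule after withdrawal.

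**The concern.** Effusion-synovitis is one of two primary endpoints, and it has a single post-baseline measurement. A rule that does not seek that measurement from early withdrawals decides, before any analysis, that part of the all-randomised population will have only a baseline scan. VAS pain is less exposed, because most withdrawals will have at least one interim score.

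The reasons for leaving early may be related to outcome. The Intervention section raises the dose over the first 4 weeks and provides for cessation on liver-enzyme thresholds, and lack of effect is a further plausible reason. Imputation from baseline data under missing at random cannot recover a dependence on what happened after baseline.

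Later withdrawals raise a second issue. A scan taken between weeks 24 and 51 is not a 52-week value by the article's own reasoning. The Introduction criticises an earlier methotrexate trial for a 6-month primary evaluation, and the Discussion justifies 52 weeks by the drug's slow onset.

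Finally, sites have three rules that give different answers for the same participant.

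**Working it through.** **1. The three collection rules compared**

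| Withdrawal pattern | Participants | Withdrawal section | Table 1 |
|---|---|---|---|
| Stops drug and leaves at week 10 | no scan sought | no scan sought | scan |
| Stops drug at week 10, leaves at week 30 | no scan sought (10 weeks' treatment) | scan attempted | scan |
| Stops drug and leaves at week 30 | scan | scan attempted | scan |

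The rules agree only in the last row.

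**2. The plan's own sample size**

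Inputs from Sample size: two-sided α 0.05, power 80%, mean 2.0 and SD 1.5 cm², 35% reduction, so Δ = 0.35 × 2.0 = 0.70 cm².

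n per arm = 2(1.96 + 0.8416)² × 1.5² / 0.70² = 72.1, so 73 by the normal approximation. The t-based solution is 73.05, so 74, as stated. For VAS (Δ = 0.20 × 50 = 10, SD 20) the t-based solution is 63.77, so 64, as stated. Dropout: 74 / 0.8 = 92.5, so 93, within the 100 enrolled.

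**3. Precision if 20% have no 52-week scan**

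With 80 per arm, SE = 1.5 × √(2/80) = 0.237. Then 0.70 / 0.237 = 2.95, and power = Φ(2.95 − 1.96) ≈ 0.84. The dropout allowance covers the lost precision.

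**4. How many have no second MRI**

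Planned dropout is 20% of 200 = 40. The share leaving before week 24 is not given. Over its full range (0 to 100%), 0 to 40 participants have no second MRI. If withdrawal is uniform over 52 weeks, the share is 24/52 = 46%: about 18 with no second scan and about 22 leaving later. If half leave early (assumption), it is 20 and 20.

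**5. Size of the possible shift**

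Assumptions: overall dropout 25% on methotrexate and 15% on placebo; half of each before week 24, so 12.5% and 7.5% without a second scan; zero change for those only; later leavers treated as measured; 100 per arm; SD 1.5 for observed change.

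*True change −0.7 versus 0:*
- Difference = 0.875 × 0.7 = 0.6125 cm².
- Variances: 0.875 × 2.25 + 0.125 × 0.875 × 0.49 = 2.022; 0.925 × 2.25 = 2.081.
- SE = √(4.104/100) = 0.2026; power = Φ(3.02 − 1.96) ≈ 86%.

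*True change −0.9 versus −0.2:*
- Difference = 0.875 × 0.9 − 0.925 × 0.2 = 0.7875 − 0.185 = 0.6025 cm².
- Variances: 0.875 × 2.25 + 0.125 × 0.875 × 0.81 = 2.057; 0.925 × 2.25 + 0.075 × 0.925 × 0.04 = 2.084.
- SE = √(4.141/100) = 0.2035; power = Φ(2.96 − 1.96) ≈ 84%.

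The identical imputed zeros shrink the variance. With the SD held at 1.5 (SE = 1.5 × √(2/100) = 0.212), power is Φ(2.89 − 1.96) ≈ 82% and Φ(2.84 − 1.96) ≈ 81%, still above 80%.

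The shift from 0.70 is 0.70 − 0.6125 = 0.0875 and 0.70 − 0.6025 = 0.0975, about 0.09–0.10 cm². Its direction as an error is unknown. If early leavers really do not change, an imputation that gives them their arm's mean change overstates the all-randomised effect by this amount. If they do change like the others, imputing zero understates it by the same amount. Without a scan the data cannot tell which.

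**The case against.** **Power.** A reader might infer that the trial falls short of its planned 80%. With 25% versus 15% dropout, that needs zero change assigned to all 40 dropouts, including those expected to have a second scan. Applied only to those without one, power stays above 80%. Zero change is also only one reading of the imputation sentence, which can equally mean a missing-at-random model using baseline covariates. This objection stands: power is not the issue.

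**Early scan used as week 52.** A reader might infer that a withdrawal scan will stand in for the 52-week value. No text says so. Table 1 gives it its own column, and how off-schedule scans enter the analysis may be settled in a statistical analysis plan that is not shown. What stands is narrower: the scan is undated, and no recall at week 52 is stated.

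**Stopping drug as leaving the trial.** The two rules concern withdrawal. The Intervention section does not call dose reduction or cessation a withdrawal, and the per-protocol threshold of more than 80% of medication implies that participants with low intake remain in the ITT set. The documents therefore do not show that everyone who stops drug loses the week-52 scan.

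**Selection by arm.** A reader might infer that methotrexate tolerators would be compared with nearly all placebo participants. The article gives one overall dropout figure and nothing by arm. A link to arm is plausible but undocumented.

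**Table 1 as shorthand.** The Participants section cites Table 1 and then qualifies the MRI, so the tick could be abbreviated. That does not reconcile treatment time with follow-up time.

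**Consent.** Full withdrawal limits what may be collected. The remedy can only ask.

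**Conclusion.** The point holds as a defect in a stated collection rule, not as missing detail. The Participants and Withdrawal sections both seek the second MRI only after a threshold, the two thresholds are measured on different clocks, and Table 1 has none. Followed as written, the two text rules leave early withdrawals without any post-baseline value for a primary endpoint that the ITT analysis claims for all randomised participants at 52 weeks. Unblinded participants are the stated exception.

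Size: about 20 of 200 without a second MRI if half of the planned dropouts leave before week 24; the possible range is 0 to 40. The possible shift is about 0.09–0.10 cm² of the planned 0.70 cm². That rests on the assumed early share, the assumed 25%/15% split and zero change in early leavers. The main consequence is a bias that cannot be checked, because scans not taken cannot be recovered in analysis. The amendment is worth making, but the documents do not support a claim that the trial is underpowered.

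**What to change.** 1. Ask every randomised participant, including those who stop study drug or withdraw at any time and still consent, to have the MRI and VAS at week 52. State separately what counts as stopping study drug and what counts as leaving the study.
2. Take an early MRI only from those who decline week-52 follow-up. Record its date and do not analyse it as a week-52 value.
3. Reconcile the Participants and Withdrawal sections with each other and with the Withdraw column of Table 1.
4. Add a sensitivity analysis to missing at random for the MRI endpoint.

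Cost: a short amendment, a site instruction and some retention effort. The week-52 MRI is already planned for every participant, and the rule for unblinded participants shows that follow-up after withdrawal is feasible. The Quality assurance section says the protocol will not be altered during the study, so that statement must be addressed when the amendment is made.

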**Fig. 1 Fig1:**
[figure not shown]
Flow chart of trial participation

**Table 1 Tab1:** Timetable and measures to be made

	Screening	Weeks						Withdraw
		0	4	12	24	36	52	
***Primary outcomes***								
MRI (effusion-synovitis volume)	✔						✔	✔
Knee pain (VAS)	✔		✔	✔	✔	✔	✔	✔
***Secondary outcomes***								
MRI (IPFP intensity alteration)	✔						✔	✔
WOMAC	✔		✔	✔	✔	✔	✔	✔
***Other measures***								
Medical history	✔							
Clinical assessment	✔							
MRI (effusion-synovitis score)	✔						✔	✔
X-ray (knee)	✔							
X-ray (lung)*	✔							
Blood tests	**✔**		✔	✔	✔	✔	✔	✔
General health status (VAS)	✔		✔	✔	✔	✔	✔	✔
SF-12	✔		✔	✔	✔	✔	✔	✔
PHQ-9	✔		✔	✔	✔	✔	✔	✔
Weight/height	✔							
Waist/hip circumference	✔							
Medication		✔	✔	✔	✔	✔	✔	✔
Tablet number		✔	✔	✔	✔	✔	✔	✔
Adverse event		✔	✔	✔	✔	✔	✔	✔

*Up to the principal investigators to decide if necessary

### Inclusion criteria

The inclusion criteria are as follows: (1) men and women, aged 45–70 years old; (2) meet the American College of Rheumatology (ACR) criteria for clinical knee OA assessed by a rheumatologist (knee pain + at least 3 of 5 that not including “no palpable warmth”) [18]; (3) knee pain on most days for at least 6 months, with a pain VAS of at least 40 mm; (4) Kellgren-Lawrence grade of 2 to 4; (5) physical examination for signs of inflammation (at least 2 of the following 4 clinical signs of inflammation: warmth over the joint area, joint margin tenderness, synovial effusion, and soft tissue swelling around the knee); (6) MRI-assessed effusion-synovitis grade of ≥ 2; and (7) able to provide written, informed consent.

